### Assessment of pain

The VAS measures the amount of pain experienced and is a pain score ranging from 0 (no pain) to 100 mm (very severe pain). Operationally, the VAS score is usually a horizontal line, 100 mm in length, anchored by word descriptors at each end. The patient marks on the line the point that they feel represents their perception of their current pain. The VAS score is then determined by measuring in millimeters from the left hand end of the line to the point that the patient marks. The VAS score will be measured at all the measurement points (baseline, 20 days of the treatment duration, 1- and 3-month follow-up).

### The X-ray measurement of cervical curvature

The schematic diagram for Borden’s method is shown in Fig. 2: in the lateral radiographs of the cervical vertebrae, line A runs between the posterosuperior margin of C2’s odontoid process and the posteroinferior margin of the C7 vertebra. A fitting curve along the posterior margin of the cervical vertebrae is line B. We define the vertical distance from the midpoint of C4 vertebra’s posterior margin to line A as the longest distance between lines A and B, which is taken as the curvature of the cervical vertebrae, line C) [9, 10].

**Fig. 2 Fig2:**
[figure not shown]
The schematic diagram for Borden’s method, which is a measure of the curvature of the cervical vertebrae

### Neck Disability Index

As a measure of neck-specific functional disability, a translated version of the original 10-item Neck Disability Index (NDI) will be used [11]. The NDI covers 10 dimensions of neck-specific disability, namely pain intensity, personal care, lifting, reading, headache, concentration, work, driving, sleeping and recreation [11]. Each item assesses one dimension and is measured on a 6-point scale from 0 (no disability) to 5 (full disability). The overall score (out of 100) is obtained by adding the score for each item and multiplying by 2 [12]. A higher score indicates greater pain and disability [13].

### Assessment of patient health status

The SF-36 questionnaire was developed with the aim of measuring CSR patients’ health status. The SF-36 consists of 36 items, 35 of which are used in the calculation of eight separate scale scores. The physical functioning scale (10 items) is the longest scale. The general health and mental health scales have five items each and the vitality and role physical scales have four items each. The role emotional scale has three items and the bodily pain and social functioning scales have two items each. The remaining item of the SF-36 is a health transition question that asks about change in general health over the past 12 months [14]. This questionnaire will be completed at all the measurement points (baseline, the last day of the treatment, 1 and 3 months after the treatment).

### Assessment of adverse events

All subjects are to be questioned about AEs during treatment at each visit point and all those reported will be analyzed regardless of the investigators’ assessments of causality. The *Medical Dictionary for Regulatory Activities* (Med DRA, Version 8.1 J) will be used to categorize reported AEs.

### Sample size considerations

We calculated the sample size for this two-arm trial on the basis of comparing BCT versus TT, using the superiority test formula:$$ {n}_1={n}_2=2{\left[\left(ta+t\beta \right)s/\delta \right]}^2, $$where *tα* and *tβ* are constants, *s* is the estimated standard difference and *δ* is the mean value of the VAS for neck pain. The patients’ numbers were arranged in equal proportion and a superiority one-sided test was employed. Setting alpha at 0.05 and beta at 0.1, the calculated sample size of each group is around 98. Considering 20 % loss to follow-up, the total sample size needed to detect this difference at a 5 % level of significance with a power of 90 % is 240 patients [15, 16].

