### Statistical analysis

The data will be collected and analyzed according to the intention-to-treat principle. Standard statistical techniques will be used to describe patients’ characteristics in both groups. We will compare baseline characteristics in both groups and, if incomparability appears, we will perform the secondary analysis, adjusting for differences. The primary outcome, VAS, will be compared between both groups using analysis of variance for repeated measures. If adjustment for possible baseline incomparability is needed, analysis of covariance will be done.

All data were analyzed statistically using SAS 9.2 version statistical software. Measurement data were expressed as mean ± standard deviation $$ \left(\tilde{x}\pm s\right) $$, and analyzed using a *t* test; rates were compared using the chi-square test. *P* < 0.05 will be used to indicated that the difference was statistically significant.

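### The sample size rests on a one-sided 5% test, but the primary analysis named is non-directional at P < 0.05 with no side stated, so the 90% power belongs to a more lenient test than the one planned

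*Protocol article*

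**What the plan says.** Two neighbouring sections of the Protocol article each fix a test.

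- **Sample size considerations.** The design calculation is directional: "a superiority one-sided test was employed. Setting alpha at 0.05 and beta at 0.1". The result follows: "the calculated sample size of each group is around 98". The closing sentence allows for 20% loss and gives the recruitment target, but drops the side: "at a 5 % level of significance with a power of 90 % is 240 patients". The formula contains a difference and a spread as symbols only. Neither has a value, and the difference is described in words as a mean: it "is the mean value of the VAS for neck pain".
- **Statistical analysis.** "The primary outcome, VAS, will be compared between both groups using analysis of variance for repeated measures". Analysis of covariance is held in reserve for baseline imbalance. Measurement data are otherwise compared by t test and rates by chi-square. A P value below 0.05 "will be used to indicated that the difference was statistically significant". The words one-sided and two-sided do not appear in this section.

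**The concern.** With two groups, the ANOVA F test for a group effect responds to the size of the difference and not to its sign. Judged at P < 0.05, it acts as a two-sided 5% test of that effect. The same is true of the analysis of covariance. The trial was thus sized for a test with a critical value of 1.645, while the named primary analysis corresponds to 1.960 for a single contrast.

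Two things are at stake:

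- **Power.** The chance of missing the assumed difference is larger than the 10% stated, if the comparison is two-sided and everything else in the design calculation is kept.
- **Reading of the result.** With the side unsettled, a result favouring balance chiropractic therapy with a two-sided P between 0.05 and 0.10 could be called significant by citing one section and not significant by citing the other. A one-sided 5% reading allows a 5% chance of falsely declaring the therapy superior. A two-sided 5% test allows 2.5% in that direction.

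**Working it through.** **Inputs.** From Sample size considerations: one-sided alpha 0.05, beta 0.1, about 98 per group, 20% loss, 240 in total. From Randomization and allocation: 1:1. Normal quantiles: 1.645 (one-sided 0.05), 1.960 (two-sided 0.05), 1.282 (90% power).

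**The plan's own figure.** The formula is n per group = 2[(z_alpha + z_beta) × s/δ]². Without values for δ and s, the 98 cannot be reproduced. It can only be inverted:

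- If 1.645 was used: δ/s = (1.645 + 1.282) × √(2/98) = 2.926/7 = 0.418 (2.926 is from unrounded quantiles).
- If 1.960 was used: δ/s = (1.960 + 1.282) × √(2/98) = 3.242/7 = 0.463.

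The allowance for loss is consistent with 240. 98 × 1.2 gives 118 per group (236 in total), and 98/0.8 gives 123 per group (246 in total). The stated total lies within 3% of both. After 20% loss, 240 × 0.8/2 = 96 remain per group.

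**Two-sided power at the implied 0.418 SD, one time point.** Power = Φ(0.418 × √(n/2) − 1.960).

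| Evaluable per group | One-sided 0.05 | Two-sided 0.05 | Two-sided, noncentral t |
|---|---|---|---|
| 96 | 89.5% | 82.5% | 82.2% |
| 98 | 90.0% | 83.3% | 82.9% |
| 120 (no loss) | 94.4% | 89.9% | 89.7% |

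For n = 98: Φ(2.926 − 1.960) = Φ(0.966) = 83.3%. The fall from 90% to 83% does not depend on δ and s. Once 98 is accepted as the one-sided 90% number, they cancel.

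**Equivalent statements for a two-sided test.**

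- Difference detectable with 90% power: 3.242 × √(2/98) = 0.463 SD with 98 per group, and 3.242 × √(2/96) = 0.468 SD with 96.
- Number needed for 90% power at 0.418 SD: 2 × (3.242/0.418)², which with unrounded values rounds up to 121 evaluable per group. Dividing by 0.8 gives 152 per group, or 304 in total.

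**How far this carries to the repeated-measures ANOVA.** The article gives neither the within-patient correlation nor the effect to be tested. As an illustration, assume 98 per group, 0.418 SD at every post-baseline visit, equal correlation r between visits, and a two-sided 0.05 test.

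- Group effect averaged over the three post-baseline visits: the variance factor is (1 + 2r)/3. Power = Φ(2.926/√((1 + 2r)/3) − 1.960), which is about 95% at r = 0.5 and about 88% at r = 0.8.
- Group main effect with baseline as a fourth level: the mean difference shrinks to 0.75 of 0.418 SD and the variance factor is (1 + 3r)/4. Power = Φ(0.75 × 2.926/√((1 + 3r)/4) − 1.960), which is about 79% at r = 0.5 and about 66% at r = 0.8.

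The 83% is therefore a like-for-like restatement of the article's own two-sample calculation. It is not the power of the ANOVA, which could lie on either side of it.

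**The case against.** The strongest reply is that the article never calls its analyses two-sided. Its only statement about sidedness is one-sided, and a t test, which it also names, can be run that way. A reader might infer that two-sided testing is stated. It is not: it follows from the named F test, strongly for the primary outcome and not at all for the t tests. What stands is that the two sections do not agree.

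A reader might also infer that the trial's true power is 83% and its type II error 17%. The documents do not support that, for three reasons:

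- The figure applies to one time point, while the primary analysis uses several.
- The 98 cannot be verified. If 1.960 was in fact used, the power is 90% two-sided at 0.463 SD, and only the description of the test is wrong.
- If all 120 per group were analysed, as the intention-to-treat statement might suggest, two-sided power would be 89.9%. Against this, the article plans for 20% loss, and the Fig. 1 caption ties each analysis to those who completed the follow-up. So 96 to 98 is its own planning basis.

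Two further inferences should not be drawn. The gap between 96 and a number given as "the calculated sample size of each group is around 98" costs 0.8 percentage points and is trivial. Nor can one assume that adjusting for baseline VAS would restore 90% power, because that rests on a baseline to follow-up correlation that the article does not give.

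**Conclusion.** The inconsistency is real and can be read directly from the two sections: the 90% power is stated for a one-sided 5% test, and the primary analysis named is non-directional at P < 0.05. Its size, for a two-sided comparison of two means at one time point, is a fall from 90% to about 83% with 96 to 98 evaluable per group. This assumes that 98 is the one-sided 90% number, with an implied difference of 0.418 SD, and that the planned 20% loss occurs. The article does not allow a power figure for the repeated-measures ANOVA. The disagreement matters mainly because it leaves open which threshold decides the trial's main conclusion.

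**What to change.** - State one side and one level for the primary test, in the same words in Sample size considerations and Statistical analysis, before the data are seen. The Trial status section describes the trial as still recruiting.
- If the test is two-sided at 0.05, as the ANOVA implies, restate the power as about 83% for a single-time-point comparison at the assumed difference. Alternatively, give about 0.46 to 0.47 SD as the difference detectable with 90% power.
- If 1.960 was used in the original calculation, correct the word one-sided instead. The 98 and the 90% then stand.
- Give the numeric difference and SD behind the 98, and describe δ as a difference between groups.

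The cost is wording in two sections. No extra patients are needed. The downside, unless 1.960 was used, is a less favourable stated power.

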### Statistical analysis

The data will be collected and analyzed according to the intention-to-treat principle. Standard statistical techniques will be used to describe patients’ characteristics in both groups. We will compare baseline characteristics in both groups and, if incomparability appears, we will perform the secondary analysis, adjusting for differences. The primary outcome, VAS, will be compared between both groups using analysis of variance for repeated measures. If adjustment for possible baseline incomparability is needed, analysis of covariance will be done.

All data were analyzed statistically using SAS 9.2 version statistical software. Measurement data were expressed as mean ± standard deviation $$ \left(\tilde{x}\pm s\right) $$, and analyzed using a *t* test; rates were compared using the chi-square test. *P* < 0.05 will be used to indicated that the difference was statistically significant.

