### Outcome measurements

The primary outcome is pain severity measured with a Visual Analog Scale (VAS) at baseline, 20 days of the treatment duration and 1- and 3-month follow-up. Secondary outcomes include cervical curvature measured using the Borden method, a composite of functional status measured by the Neck Disability Index (NDI), patient health status (evaluated by the SF-36 health survey) and adverse events (AEs) as reported in the trial.

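### Adjustment for baseline VAS depends on an undefined look at baseline balance, and the plan does not settle whether the adjusted analysis is secondary or replaces the primary one

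*Protocol article*

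**What the plan says.** The Statistical analysis section of the Protocol article makes three statements on this point.

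- Baseline characteristics are compared between the groups and "if incomparability appears, we will perform the secondary analysis, adjusting for differences".
- VAS, the primary outcome, is compared between groups by repeated-measures analysis of variance.
- Directly after that: "If adjustment for possible baseline incomparability is needed, analysis of covariance will be done".

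Nothing defines incomparability or says when adjustment counts as needed, and no covariate is named. The section states neither which visits enter the repeated-measures analysis nor which term is tested.

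The Outcome measurements section lists VAS "at baseline, 20 days of the treatment duration and 1- and 3-month follow-up". The section on population and recruitment places baseline VAS before randomisation, so it is scheduled for every participant. Allocation is central and 1:1 (Randomization and allocation).

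**The concern.** Under central randomisation, a baseline difference between the arms is a chance event. Whether to adjust should depend on how well baseline VAS predicts later VAS, which can be judged in advance, and not on how balanced the arms turn out to be. The article states the opposite rule, so this is not a detail left to a statistical analysis plan.

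The two sentences on adjustment allow two readings, and each has a fault.

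- If ANCOVA is only secondary, the unadjusted result stays primary even when the arms differ at baseline, which is where it is least trustworthy.
- If ANCOVA replaces the ANOVA, the data choose the primary model through a trigger that nobody has defined.

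On both readings, baseline VAS is left out of the primary model whenever balance looks acceptable, and precision is lost.

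**Working it through.** **The plan's own figure.** The Sample size section says: "Setting alpha at 0.05 and beta at 0.1, the calculated sample size of each group is around 98", and "a superiority one-sided test was employed". It gives no number for s or δ, so 98 cannot be reproduced forwards. Solved backwards, δ/s = (1.645 + 1.282) × √(2/98) = 2.926/7 = 0.418. All power figures below use this effect.

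**Assumptions not in the documents.** Equal SD at every visit; equal correlation ρ between all visits, shown at 0.3, 0.5 and 0.7; the same effect at the three follow-ups; 98 per arm analysed.

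**Formula.** With variance v (in units of s²), one-sided 0.05 power = Φ(0.418 × 7/√v − 1.645).

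- Single visit: unadjusted v = 1; ANCOVA v = 1 − ρ².
- Mean of three follow-ups: unadjusted v = (1 + 2ρ)/3; ANCOVA v = (1 + 2ρ)/3 − ρ².

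Example, single visit, ρ = 0.5: v = 0.75, 2.926/0.866 = 3.379, minus 1.645 is 1.734, giving 95.9%.

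| Analysis | ρ = 0.3 | ρ = 0.5 | ρ = 0.7 |
|---|---|---|---|
| Single visit, unadjusted | 90.0% | 90.0% | 90.0% |
| Single visit, ANCOVA | 92.3% | 95.9% | 99.3% |
| Mean of three follow-ups, unadjusted | 99.1% | 97.4% | 94.8% |
| Mean of three follow-ups, ANCOVA | 99.7% | 99.8% | >99.9% |

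For 90% power, a single visit needs 98 per arm unadjusted against 90, 74 and 50 with ANCOVA. The mean of three follow-ups needs 53, 66 and 79 against 44, 41 and 31.

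**If baseline is one of the ANOVA visits.** This is possible but not stated.

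- Group main effect over four visits: the effect shrinks to 0.75 × 0.418 and v = (1 + 3ρ)/4. Power is 93.8%, 87.1% and 80.2%.
- Group-by-time: noncentrality = 49 × 0.75 × 0.418²/(1 − ρ), 3-df F test at 0.05. Power is 71.7%, 86.4% and 98.2%.

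**Behaviour under a chance imbalance.** Take a baseline difference just at two-sided 0.05: 1.96 × √(2/98) = 0.28 SD. With no treatment effect, the expected unadjusted follow-up difference is ρ × 0.28 = 0.08, 0.14 and 0.20 SD, which is 20%, 33% and 47% of the implied effect.

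A simulation (40,000 null replicates, two-sided 0.05) assumed that ANCOVA is triggered by baseline VAS p < 0.05, and that the analysis is otherwise the group main effect with baseline as a visit.

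- Among null trials with a significant baseline difference, the unadjusted main effect rejected in 32%, 45% and 53%; ANCOVA rejected in about 4% to 6%.
- Overall type I error of the two-stage rule was 3.5%, 3.2% and 2.5%.

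**The case against.** The strongest defence is that the plan does name an unconditional primary method, repeated-measures ANOVA, and calls the adjusted analysis secondary. A reader might infer that the primary model itself is chosen by the data. The text does not establish this: only the later ANCOVA sentence can be read as replacement. What stands is that the two sentences leave the matter open.

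A reader might also infer that baseline VAS enters the ANOVA as an outcome visit and dilutes the group effect. The Outcome measurements section allows that reading, but it lists measurement times, and the Statistical analysis section names neither the visits nor the tested term. The dilution figures are therefore conditional. With group-by-time as the test, the pattern reverses and power rises with ρ. A contrast of the follow-up mean minus baseline, with v = (1 + 2ρ)/3 + 1 − 2ρ, gives 91.7%, 97.4% and 99.9%. ANCOVA on the follow-up mean still exceeds each of these, at 99.7%, 99.8% and above 99.9%.

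Three further limits stand.

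- Under the assumed trigger, overall type I error falls, so there is no case for alpha inflation.
- Computing the unadjusted single-visit comparison at two-sided 0.05 gives 83%. That combines an effect derived from a one-sided test with a two-sided test, so it does not show a shortfall against the planned 90%.
- Entry requires a VAS score above 4 and below 8. This narrows baseline variation and may lower the correlation. At ρ = 0.2 the single-visit gain is about 1 point (90% to 91%). It also makes equal SDs doubtful.

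Finally, the plan does not say that baseline balance is judged by a significance test, or that VAS is the variable judged. The p < 0.05 trigger is an assumption.

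**Conclusion.** The point holds as a weakness in efficiency and prespecification, not as a failure of overall error control. Adjustment is conditional on an undefined judgement of balance, and the standing of the adjusted analysis is unresolved.

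Under the stated assumptions, always adjusting gains about 2, 6 and 9 percentage points of power at a single visit for ρ of 0.3, 0.5 and 0.7, and about 1, 2 and 5 points for the mean of three follow-ups. The entry window makes the lower values more plausible. The loss would be larger if the test were the four-visit group main effect, which the document does not state. Apart from power, an unadjusted primary result would mislead in the trials where the arms differ by chance at baseline, and those are the trials in which the plan does not say which result governs.

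**What to change.** Delete the conditional rule. Prespecify one primary model for VAS, either a mixed model for repeated measures or ANCOVA, with:

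- the follow-up visits as the responses;
- baseline VAS as a covariate for every participant, whatever the observed balance;
- a named treatment contrast, at one visit or averaged over stated visits.

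Keep the baseline table as description only, with no bearing on the choice of model.

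The cost is a change of wording before the data are analysed. The Trial status section reports that recruitment was still under way at submission, so the data cannot be taken as already complete. Baseline VAS is already scheduled for every participant, so no extra visit, measurement or patient is needed.

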## Background

Cervical spondylosis is a very common disorder and cervical spondylotic radiculopathy (CSR) is one of the most common patterns, accounting for about 60 to 70 % of all cervical spondylosis [1–3]. The incidence of CSR tends to increase year by year due to population aging, lifestyle changes and work or life stress. Its clinical manifestations focus on pain and numbness of the neck and arm as well as restricted movement of the neck, which greatly affect people’s lives and work. The agents currently approved for treatment and/or prevention of CSR include operative treatment and nonoperative treatment categories (including drugs, traction, manipulation, physical therapy, functional exercise, etc.), but many studies have confirmed that nonoperative therapy has more evident effects on the optimized scheme of CSR [4–6]. Among them, manipulation is the most common therapy for CSR due to its low risk, good therapeutic effect, ease of operation and its economics [7, 8]. However, as there are many kinds of manipulations with different efficacy standards, treatment and operation standardization and evaluation mechanisms, it is not conducive to the long-term development of massage, which could result in the problem of choice and multiple choices easy to cause medical information source waste. Moreover, there are currently few randomized, parallel-controlled trials to verify its efficacy in treating CSR.

From this we have developed a balance chiropractic therapy (BCT) to treat CSR, which has been clinically examined as effective at curing CSR for more than 50 years, and we examine the therapeutic effect and safety of BCT to improve the syndrome experienced by CSR patients in a multicenter, randomized, parallel-controlled trial. The results of this study will provide evidence regarding the value and safety of BCT as an intervention to improve the syndrome in CSR-affected individuals. Furthermore, we speculate the mechanisms of action can be partially identified by this study.

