### Treatment group

In the treatment group, patients are requested to be in the sitting position and receive the following treatments: (1) balancing tendon-regulation: a to-and-fro kneading motion is applied three times to relax the muscles in the nuchal midline: splenius capitis, splenius cervicis and the trailing edge of sternocleidomastoid, respectively. Then manipulations of plucking and relaxing the tendons are applied five to seven times over the same area with a force that the patients can tolerate. Finally, rolling the region along the upper back of bladder meidian for five to seven times, (2) balancing osteopathy: firstly, with the patient adopting an upright sitting position, the practitioner holds the patient’s occiput and jaw between his hands and pulls upward forcefully for 9 s and then relaxes for 3 s. While stretching the neck, the physician turns the patient’s head to the front, back, left and right at an angle of roughly 45° three times and then obliquely wrenches the neck at the position that corresponds with the pathological features of the clinical examination and X-rays; if the lesion sites are at C1 to C3, or C4 to C6, or C7 to T1 within the cervical spine unit, the neck will be flexed at 15°, 0°, or 30 to 45°, respectively. The patient then repeatedly rotates their neck to left or right side to roughly 40° degrees on its own at the stretching state of cervical vertebra, and then rotates toward the affected side to the limit of the angle as well as bending the neck forward while the physician gives a vertical pulling and extending force to the patient’s neck. One or more snapping sounds will be heard if the procedure has been successful, (3) balance collaterals-dredging: first, holding the participant’s upper limb and then quickly shaking that upper limb up and down forcefully with a low-amplitude jittery motion, repeated three times. Next, for the ear-lifting method, kneading-pressing and pulling with the thumb and forefinger are then applied to the region of the upper, middle and lower three parts of the helix, respectively, for 30 s with a force that the patient can tolerate. Lastly, pressing with the thumb is repeatedly applied five to seven times along the DU meridian with focus on the acupoints DU4 (*Mingmen*), DU14 (*Dazhui*), DU17 (*Naohu*) and DU20 (*Baihui*).

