### Control group

In the control group, patients will received TT. The patient is sitting comfortably and wearing a cloth bag for occipital-jaw traction, with their head bending forwards at an angle of about 10–15°. The traction weight for cervical spondylosis starts at 3 kg and gradually increases to the maximum weight of 6 kg in increments of 0.5 kg each time. The treatment is performed 30 min at a time every other day for a total of 10 times in 20 days.

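### The sample size and the named tests treat all patients as independent; if outcomes of the hand-delivered balance chiropractic therapy (BCT) differ between practitioners, the standard error is too small and power falls below the stated 90%

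*Protocol article*

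**What the plan says.** Sample size considerations uses the two-independent-means formula, n per group = 2[(tα + tβ)s/δ]², and reports: "Setting alpha at 0.05 and beta at 0.1, the calculated sample size of each group is around 98". It adds that "a superiority one-sided test was employed". With 20% loss the total is 240 at 90% power. No numbers are given for s or δ, and no design effect, ICC or number of practitioners appears.

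Statistical analysis states: "The primary outcome, VAS, will be compared between both groups using analysis of variance for repeated measures". It adds analysis of covariance if baselines differ, and t and chi-square tests. Its significance rule is P below "0.05 will be used to indicated that the difference was statistically significant", with the side of the test not stated. No practitioner or centre term is named. Randomization and allocation mentions a stratification factor without naming it.

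On delivery, Treatment group describes a manual technique in which the physician "obliquely wrenches the neck at the position that corresponds with the pathological features of the clinical examination and X-rays" and judges success by an audible snap. Control group describes cloth-bag traction: "The traction weight for cervical spondylosis starts at 3 kg and gradually increases to the maximum weight of 6 kg". Recruitment is at four hospitals.

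**The concern.** When a treatment is delivered by hand, patients of the same practitioner may do more alike than patients of different practitioners. Here that would arise mainly in one arm, because traction is applied by weights in stated steps. Repeated-measures ANOVA handles correlation between visits of one patient. It does not handle correlation between patients who share a practitioner, and neither does the t test or the sample-size formula.

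If such a practitioner effect exists, the BCT mean is estimated less precisely than the analysis will report. A difference driven by a few practitioners could then pass as a general effect of BCT, and the stated 90% power would be optimistic. The trial is meant to support BCT as a therapy for wider use, so inference beyond the practitioners who happened to take part matters.

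**Working it through.** **Inputs from the protocol article:** about 98 per group, 1:1 allocation, one-sided alpha 0.05, power 90%.

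**Assumptions, because the article gives no figures:** k = 4 to 12 BCT practitioners with equal caseloads; ICC = 0.01 to 0.05 in the BCT arm; ICC = 0 under traction; same total variance in both arms.

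**Step 1: the plan's own figure.** Without s and δ, the 98 cannot be reproduced independently. Solving backwards, 98 = 2[(1.645 + 1.282)s/δ]² gives δ/s = 2.926 × √(2/98) = 0.418. The 90% therefore holds at δ/s = 0.418 with an ICC of exactly 0.

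**Step 2: clustering in the BCT arm only.**
- Design effect: DE = 1 + (98/k − 1) × ICC
- Variance multiplier for the group difference: v = (1 + DE)/2
- One-sided power with a correct standard error: Φ(2.926/√v − 1.645)
- True error of the independence test: 1 − Φ(1.645/√v) one-sided, or 2[1 − Φ(1.96/√v)] two-sided

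Worked case, k = 4 and ICC = 0.05: DE = 1 + 23.5 × 0.05 = 2.175; v = 1.5875; √v = 1.26. Power = Φ(2.323 − 1.645) = 75.1%. One-sided error = 1 − Φ(1.306) = 9.6%. Two-sided error = 2[1 − Φ(1.556)] = 12.0%.

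| k | ICC | DE | v | Power, one-sided | Error, one-sided 5% test | Error, two-sided 5% test |
|---|---|---|---|---|---|---|
| 12 | 0.01 | 1.07 | 1.04 | 89.1% | 5.3% | 5.4% |
| 12 | 0.05 | 1.36 | 1.18 | 85.3% | 6.5% | 7.1% |
| 8 | 0.02 | 1.23 | 1.11 | 87.1% | 5.9% | 6.3% |
| 8 | 0.05 | 1.56 | 1.28 | 82.7% | 7.3% | 8.3% |
| 4 | 0.01 | 1.24 | 1.12 | 86.9% | 6.0% | 6.4% |
| 4 | 0.05 | 2.18 | 1.59 | 75.1% | 9.6% | 12.0% |

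**Step 3: small-sample degrees of freedom.** The powers above use normal quantiles, which flatter a design with few practitioners. Satterthwaite degrees of freedom are (DE + 1)²/[DE²/(k − 1) + 1/97]. For k = 4 and ICC = 0.05 this is 3.175²/(2.175²/3 + 1/97) = 6.35. The one-sided critical value becomes 1.924 instead of 1.645. Noncentral-t power with noncentrality 2.323 is then about 66%. For k = 12 and ICC = 0.01 the degrees of freedom are about 37 and power is about 88%.

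**Step 4: what restoring 90% by size alone would take.** With normal quantiles, n per arm = (2 − ICC)/(2/98 − ICC/k). At ICC = 0.05, after allowing for 20% loss, the totals are 302 (k = 12), 346 (k = 8) and 618 (k = 4), against 246 from the same calculation with no clustering.

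**The case against.** **The premise is not documented.** Nowhere does the article say that BCT results vary by practitioner. This stands, and it is why the point is conditional. A reader might infer that the error bars are certainly too narrow and the power certainly too high; the article supports neither as a fact.

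**The Background does not supply the missing evidence.** Its remark that "there are many kinds of manipulations with different efficacy standards, treatment and operation standardization and evaluation mechanisms" may tempt a reader to see an admission of operator variation. It concerns differences between kinds of manipulation, not between practitioners of BCT, and should not be cited for this.

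**BCT is partly standardised and traction is not wholly fixed.** Pull times, repetitions and flexion by lesion level are specified for BCT, and force in the tendon and ear work is bounded by patient tolerance. The traction weight rises in steps and the head angle is approximate. If the same staff run both arms, some of any effect is shared and cancels. This is fair: zero clustering under traction is an assumption.

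**An article leaves model detail to the analysis plan.** True of a random-effect term alone. But this text names its primary test and gives an unqualified 90% from a formula that assumes independence. A later model term would not correct that power statement.

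**A centre term would deal with it.** None is stated. One would absorb whatever both arms of a hospital share. With four practitioners, one per hospital is the natural reading; practitioner and hospital then coincide in the BCT arm, so it cannot be argued generally that the effect lies within hospital. A component specific to BCT would still remain after a common centre effect.

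**Inference could be limited to these practitioners.** That is a defensible target, and for it the stated standard error need not be too small. The criticism applies to inference beyond them.

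**Conclusion.** The point holds conditionally. The formula and every named test treat patients as independent, and for any positive practitioner ICC in the BCT arm the standard error for wider inference is too small and power is below 90%. The direction is firm; the size is not known.

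On the stated assumptions the consequence ranges from negligible (12 practitioners, ICC 0.01) to material (4 practitioners, ICC 0.05). The 12.0% error should not be read as that of the plan's own test: it applies only if the P < 0.05 rule is two-sided, and the matching figure for the one-sided test in the sample-size section is 9.6%. Nor do the figures show that the trial must be enlarged, since the low end of the range needs almost nothing.

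**What to change.** 1. Record the treating BCT practitioner for every patient. Do this now: the article reports that recruitment is under way, and the information may not be recoverable later.
2. Keep the stated primary analysis. Beside it, pre-specify a sensitivity analysis of VAS using a partially nested mixed model, with a practitioner random effect in the BCT arm and small-sample degrees of freedom, and report both results together.
3. In Sample size considerations, state that 90% power assumes no practitioner clustering, give the actual number of BCT practitioners, and show power over a range of plausible ICCs.

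The cost is one data field, one pre-specified model and a sentence or two of text. No patients are added, so any lost power is accepted and disclosed rather than recovered. The downside is a wider and less stable interval in the sensitivity analysis when practitioners are few.
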